### Statistical methods

For primary outcomes, t-tests and Wilcoxon tests will be used to compare the age and severity of X(T) of those participants retained with any withdrawing from the trial and to compare those who consent with those eligible but refusing to participate. A chi-square test will be carried out to assess the variability of the primary outcome (difference in cure rate at the final assessment between the surgery and active monitoring arm).

For secondary outcomes, non-parametric testing (Wilcoxon) will be used to compare change over time in median control scores within the two groups between baseline and 9-month follow-up (Mann-Whitney tests will examine any differences between the groups at baseline and 9 months); rates of development of amblyopia in the two groups will be determined by monitoring visual acuity at the 3-, 6- and 9-month assessments. For the QOL measurements, we are primarily concerned with response and completion rates for these instruments in both groups; in addition, their validity will be assessed by matching individual pre- and post-treatment scores to the post-treatment primary outcome using t-tests.

Statistical significance will be set at *p* < 0.05. Data will be analysed with the SPSS statistical package.

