### Recruitment and consent

Children referred from community screening, general practice or other health professionals are clinically assessed in the normal way when they attend their initial outpatient visit. Where appropriate, glasses are prescribed to correct any refractive error. Discussion about the management of the X(T) itself includes providing information about the study and the possibility of taking part. Parents who express an interest are then given written information and subsequently telephoned by a member of the study team to discuss any queries they may have once they have had time to read the documentation and talk things through with their families. All parents are given an appointment on a study recruitment clinic. At the recruitment clinic, eligibility is confirmed by checking the results of the initial routine clinical assessment against the inclusion criteria. Eligible parents are then asked if they would like to enter the study. Informed consent is obtained from those who decide to participate. Participants are also being identified from existing lists of patients who are already under follow-up and fulfil the eligibility criteria; we are adhering to the same information-giving and consent procedures as for new referrals.

The following routine clinical assessments are made in order to confirm the patient’s eligibility for the trial:

• BSV testing;

• Best corrected VA on an age-appropriate test;

• Measurement of the ocular misalignment using the APCT;

• Measurement of how well the squint is controlled using the NCS and Mayo scores.

Eligible families who do not wish to take part in the trial are asked whether they would consent to come back for a follow-up appointment after 9 months and allow us to use routine clinical data from that visit and their initial visit. Data from those who agree to this will be used to verify whether the recruited group is representative and to determine how many of those eligible but not recruited went on to have surgery during that 9-month period.

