### Randomisation

Randomisation is in permuted blocks stratified by collaborating centre, age and severity of X(T) as measured by the NCS. A blocked allocation (permuted random blocks of variable length) system is being used to allocate patients to the two groups in a 1:1 ratio to intervention (surgery) and control (active monitoring) groups. Randomisation is administered using a centralised, password-protected web-based system, which is managed by the Newcastle Clinical Trials Unit (NCTU). The PI at site, or individual with delegated authority, enters the patient ID, initials and the stratifying variables, which then return the allocation status. Participants are informed of their group allocation and given the appropriate Group Allocation Information sheet.

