### Proposed outcome measures

For children with X(T), and their parents, the most relevant outcome from intervention is the restoration of normal eye alignment, with associated cosmetic and functional benefits. The primary outcome in a full-scale trial will therefore be the difference in the cure rate of X(T) between the surgical and actively monitored group; this is also the primary outcome for which data will be collected in the current pilot in order to inform sample size calculations for a definitive RCT. Cure will be defined as:

• a control score (NCS) of 0 (misalignment never noticed by parents, no observable deviation on cover test)

• demonstrable near stereoacuity in children over 3 years of age

Secondary outcomes include age-specific QOL assessments, median scores of control of exotropia assessed by parental report and clinical components of the NCS and the Mayo Score, rates of amblyopia, use of health-care resources, NHS costs, costs to families accessing the treatments being evaluated and incremental cost per cured patient (with cure as defined by the primary outcome), and a cost-consequences analysis based on the incremental cost with respect to changes in all relevant outcomes where possible.

The key outcomes of this pilot study are:

• data on the variability of the primary and secondary outcome measures;

• rates of participant recruitment and randomisation;

• nature and extent of participation bias;

• rates of cross-over and retention of recruited participants;

• nature and extent of biases arising from cross-over or loss to follow-up.

An initial recruitment rate of >60% and a retention rate of >70% will be considered necessary to indicate feasibility of a full-scale RCT.

Our intention in the full trial would be to conduct a cost-effectiveness analysis based on incremental cost per cured patient (as defined by the primary outcome) and a cost-consequences analysis based on incremental cost with respect to changes in all relevant outcomes where possible, including the QOL measure and different clinical measures. In the pilot study, we will rehearse this cost-effectiveness analysis to inform the study hypothesis and the analysis plan for the definitive trial. We will also assess the ease of collecting information on outcome and costs needed for the health economics analysis.

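### Bias from loss to follow-up is a key pilot outcome, but the only analysis stated for it compares leavers and stayers on age and severity, which cannot show bias in the cure-rate difference

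*Protocol article*

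**What the plan says.** **Aim.** Proposed outcome measures lists, as a key outcome of the pilot, the "nature and extent of biases arising from cross-over or loss to follow-up". Rates of cross-over and of retention are listed there as a separate item.

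**Analysis.** Statistical methods uses t-tests and Wilcoxon tests to "compare the age and severity of X(T) of those participants retained with any withdrawing from the trial". The same sentence uses the same two variables "to compare those who consent with those eligible but refusing to participate". No split by allocated arm is stated. Significance is set at p < 0.05.

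**Severity.** Randomisation is "stratified by collaborating centre, age and severity of X(T) as measured by the NCS", so I read age and severity in the analysis sentence as values at entry. The sentence itself does not say so.

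**Outcome that loss could bias.** The clinical primary outcome is the "difference in cure rate at the final assessment between the surgery and active monitoring arm". Cure requires a Newcastle Control Score (NCS) of 0 and, in children over 3 years, demonstrable near stereoacuity.

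**Data that could inform the question.** Clinical tests has the NCS, Mayo score, alignment, acuity and binocular testing done at every visit, and the Abstract places visits at 3, 6 and 9 months. Under Recruitment and consent, eligible families who decline are invited to "consent to come back for a follow-up appointment after 9 months and allow us to use routine clinical data from that visit". The stated purpose is to "verify whether the recruited group is representative and to determine how many of those eligible but not recruited went on to have surgery" within those 9 months.

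**The concern.** The aim and the analysis do not meet. Loss biases the cure-rate difference when children who leave differ in outcome from those who stay, and differ in a way that depends on the arm. A comparison of age and severity, not split by arm, looks at neither. Two groups can match on both variables and still have different cure rates.

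Informative loss is plausible here. Parents know the allocation, and the Background describes substantial default from follow-up in routine care. A surgery-arm family might leave to avoid the operation, or a monitored family might go elsewhere to have it. If surgery status is not sought for families who leave, some cross-over may be recorded only as loss, and the cross-over rate, itself a key outcome, would be too low.

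The pilot's cure rates are meant to inform the sample size of the definitive trial. A non-significant comparison on age and severity in a small group of leavers could be taken as evidence that loss was harmless when it shows nothing of the kind.

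**Working it through.** **1. The plan's own figure on loss.** Participants and sample size gives a standard error of at most 4.3% for 6-monthly attrition, with half of 240 families recruited (n = 120).
- Formula: SE = √(p(1−p)/n).
- Worst case, p = 0.5: √(0.25/120) = 4.56%, slightly above 4.3%.
- At p = 0.30: √(0.21/120) = 4.18%. The stated bound holds for attrition up to about 33%.

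This figure concerns how many leave, not what bias their leaving causes. The point here does not depend on it.

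**2. Expected number lost.** The Abstract's target is 144 recruited and 120 retained: 144 − 120 = 24 lost, and 24/144 = 16.7%. At the 70% retention mark in Proposed outcome measures, 0.30 × 144 ≈ 43 are lost and 101 retained.

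**3. What the stated comparison can detect.** For a two-sided 5% test (sidedness is not stated, so this is an assumption) with 80% power, the detectable difference in SD units is (1.96 + 0.842) × √(1/n₁ + 1/n₂).

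| Retained / withdrawn | √(1/n₁ + 1/n₂) | Detectable at 80% power | Power for 0.5 SD |
|---|---|---|---|
| 120 / 24 | 0.224 | 0.63 SD | 61% |
| 101 / 43 | 0.182 | 0.51 SD | 78% |

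**4. Why pooling can hide the problem.** Suppose, as an assumption, that 12 children leave each arm. Surgery-arm leavers are 0.5 SD milder than stayers, and monitored leavers 0.5 SD more severe. The pooled difference is (12 × (−0.5) + 12 × 0.5)/24 = 0. The comparison finds nothing, although loss has made the retained arms differ.

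**5. Why age and severity do not bound the bias in cure.** Take 72 children per arm, 60 retained in each, and assumed observed cure rates of 30% and 10% (18 and 6 cured). The observed difference is 20 points.
- If no lost surgery-arm child and every lost monitored child is cured: 18/72 − (6 + 12)/72 = 0 points.
- If the reverse: (18 + 12)/72 − 6/72 = 33 points.

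Both extremes are compatible with leavers and stayers identical in age and severity. The width, 2 × 16.7 = 33 points, follows from the loss fraction alone. It illustrates that outcome-type data are needed and does not measure a defect particular to this trial.

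**6. Which data exist and where they are used.**

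| Data | Collected or sought | Assigned to the withdrawn-versus-retained comparison |
|---|---|---|
| Age, severity | Yes | Yes |
| Control scores at 3 and 6 months | Yes, for children seen then | Not in the text shown |
| Routine 9-month data | From consenting decliners | Not in the text shown |
| Surgery status | To be determined for decliners who agree | Not in the text shown |

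Binocular testing may be by stereovision or by motor fusion, so near stereoacuity may be missing at some interim visits.

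**The case against.** The strongest reply is that this is a condensed article. Withdrawal procedures, optional consent items and further analyses may sit in the full protocol, the consent form or an analysis plan. This stands as far as the data route is concerned: its absence from the article is not an error. It does not remove the mismatch, because the article states both the aim and the test chosen for it.

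Second, a reader might infer that bias on the outcome cannot be seen at all, or that a child who leaves has no record of control or surgery. The documents do not support this. Children who leave after the 3- or 6-month visit have control scores, and only those lost before 3 months have no post-baseline assessment. Nothing in the article says that records go unchecked after withdrawal.

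Third, a monitored family wanting surgery need not leave. Clinic appointments and Potential risks and adverse events both allow surgery on parental request if the clinical team agrees, and cross-over and retention are already listed as separate rates. This stands, and it narrows the hidden cross-over to families who stop visits or go elsewhere.

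Fourth, the contrast with decliners can be overdrawn. The stated tests treat decliners and withdrawers alike, on the same two variables. Decliners are asked for a visit because they otherwise have no trial follow-up. The difference lies in data collection, not in analysis.

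Finally, the pilot is explicitly not powered for the difference between arms. That is true, but describing bias from loss is an aim the pilot sets itself.

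**Conclusion.** The point holds as a mismatch between a stated key outcome and the analysis stated for it. A comparison on age and severity, with no split by arm, cannot show whether loss biases the cure-rate difference. Even for what it does examine, it has 80% power only for about 0.63 SD at the planned loss (0.51 SD at the 70% retention mark).

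This rests on reading severity as the NCS at entry, on a two-sided 5% test, and on the retention target in the Abstract. If severity meant a later NCS, the comparison would come closer to the outcome but would still lack arm and surgery receipt.

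A reader might also infer that collecting routine data from half of the leavers would halve the worst-case limits on the cure-rate difference. That is not supported. The recovery fraction would be an assumption, and unmasked routine data cannot stand in for the masked 9-month assessment, so the limits on the primary outcome as defined would not narrow.

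**What to change.** 1. In Statistical methods, compare withdrawn with retained children **by allocated arm** on last available NCS, last available near stereoacuity and surgery receipt, in addition to age and severity.
2. Report these as estimates with confidence intervals, not as tests. By arm the numbers are about 12 against 60, and the detectable difference rises to 2.80 × √(1/60 + 1/12) = 0.89 SD, so a p-value would say little.
3. Offer families who stop trial visits the same optional consent that decliners are offered: use of routine clinical data at about 9 months, and whether and when surgery took place. For families already enrolled, ask when they stop visits.
4. Count a known cross-over among them as a cross-over as well as a loss.

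The first two changes need no new data, apart from surgery status for children who have left. The third costs one optional consent item and a record look-up by existing site staff, under a procedure already run for decliners. The routine data come from unmasked clinicians and will be incomplete, particularly for families who leave care altogether. They serve the bias assessment only and do not replace the masked primary outcome.

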**Discussion:**

The SamExo pilot trial will provide important pointers regarding the feasibility of a full RCT of immediate surgery versus deferred surgery/active monitoring. The results of this pilot, including differences in cure rates, will inform the design of a definitive RCT.

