### Participants and sample size

Children aged between 6 months and 16 years referred to the clinics with suspected X(T) from community screening, general practice or other health-care professionals, and subsequently diagnosed with X(T), as well as existing patients fulfilling the eligibility criteria. The parent/guardian provides written informed consent for participation in the study prior to any trial-specific procedures.

A formal power calculation was not performed for this feasibility study. It is not powered to detect a clinically or economically meaningful difference in the primary outcome between the surgical and active monitoring groups. Rather, the aim is to provide robust estimates of the likely rates of recruitment and retention, and to yield estimates of the variability of the primary and secondary outcomes to inform power calculations for a subsequent full-scale RCT. We originally estimated that over a recruitment period of 6 months (subsequently extended to 9 months) across four centres, we would be able to approach 240 patients who met the entry criteria. From their responses we would be able to determine whether the study is acceptable to parents and consequently whether it is possible to recruit patients and follow them up. We would also be able to estimate attrition rates. By approaching 240 children/parents we would be able to estimate the recruitment rate with a standard error no larger than 3.3%. Assuming that half of these children are actually recruited, we will be able to estimate the 6-monthly attrition rate with a standard error no larger than 4.3%.

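### The chi-square test named for the cure rate cannot assess its variability, so the stated analysis does not match the pilot's estimation aim

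*Protocol article*

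**What the plan says.** All references are to the protocol article.

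- **Statistical methods** names one between-arm analysis of cure: "A chi-square test will be carried out to assess the variability of the primary outcome". A parenthesis explains the outcome as the "difference in cure rate at the final assessment between the surgery and active monitoring arm". The section then adds: "Statistical significance will be set at *p* < 0.05". It names no estimate or interval for the cure rates or their difference.
- **Participants and sample size** states: "A formal power calculation was not performed for this feasibility study". It says of the study: "It is not powered to detect a clinically or economically meaningful difference in the primary outcome between the surgical and active monitoring groups". Part of the aim is instead "to yield estimates of the variability of the primary and secondary outcomes to inform power calculations for a subsequent full-scale RCT".
- **Abstract (Methods)** and **Proposed outcome measures** repeat that purpose. The second puts variability of the outcome measures first among the pilot's key outcomes.
- **Abstract (Discussion)** says: "The results of this pilot, including differences in cure rates, will inform the design of a definitive RCT".
- **Randomisation** says: "Randomisation is in permuted blocks stratified by collaborating centre, age and severity of X(T) as measured by the NCS".

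**The concern.** The sentence gives a method and a purpose that do not belong together. A chi-square test returns a statistic and a p-value for the hypothesis of equal proportions. It measures neither the variability of a binary outcome nor the precision of a difference. For a binary outcome the variance in each arm is p(1 − p), so the useful outputs are the two cure rates, their difference, and the uncertainty of each.

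This is a wrong statement about what a named method does, so it is not a detail that an unseen analysis plan could be expected to supply. It also sits badly with the sample size section, which declines to power the study for this difference and asks for estimates. If the sentence is followed literally, the headline cure result is a verdict at p < 0.05. A planner would then have no stated interval showing how loosely the pilot fixes the rates.

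**Working it through.** **Inputs from the article.** 120 children retained at the 9-month visit (Abstract, Methods) and 1:1 allocation (Randomisation), so about 60 per arm. Alpha is 0.05, taken as two-sided because the article does not say. It gives no expected cure rates, so every cure rate below is an assumption.

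**1. The plan's own precision figure.** For recruitment, the sample size section gives a standard error of at most 3.3% from 240 families approached. The worst case is √(0.5 × 0.5 / 240) = 3.23%, so the figure reproduces. The authors planned recruitment by precision; no matching figure is given for cure.

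**2. The same calculation for cure, worst case (p = 0.5).**
- One arm, n = 60: SE = √(0.25/60) = 6.5 points.
- Difference: SE = √(0.25/60 + 0.25/60) = 9.1 points; 95% half-width = 1.96 × 9.13 = 17.9 points.
- If all 144 recruited children were assessed (72 per arm): half-width 16.3 points.
- If 120 were recruited and 70% retained (42 per arm): half-width 21.4 points.

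**3. An assumed case, 15% v 35%.** SE = √(0.15 × 0.85/60 + 0.35 × 0.65/60) = √(0.002125 + 0.003792) = 7.7 points. The half-width is 1.96 × 7.69 = 15.1 points, so the interval is 4.9 to 35.1 points.

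**4. What the p-value leaves out.** Two possible tables with 60 per arm (Pearson chi-square, no continuity correction):

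| Monitoring v surgery | p | Difference | SE | 95% CI |
|---|---|---|---|---|
| 8/60 v 15/60 | 0.104 | 11.7 | 7.1 | −2.3 to 25.6 |
| 25/60 v 34/60 | 0.100 | 15.0 | 9.0 | −2.7 to 32.7 |

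The p-values are almost the same, but the control rates are 13% and 42%, and the control-arm variances p(1 − p) are 0.116 and 0.243. For a fixed target difference the control rate matters a great deal. At 80% power, a 10-point difference needs 199 per arm for 10% v 20% and 388 per arm for 40% v 50%.

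**5. Power of the named test at 60 per arm.** 33% for 10% v 20%, 45% for 20% v 35%, 61% for 30% v 50%, 72% for 15% v 35% and 79% for 10% v 30%. This agrees with the article's statement that the study is not powered for the difference, though a 20-point effect would be detected more often than not at these rates.

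**The case against.** The strongest reply is that this is loose wording and little is lost.

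- **The estimates will exist anyway.** The 2x2 table behind the test shows both cure rates, and the variance of a binary outcome follows from them. The planned rehearsal of incremental cost per cured patient also needs cure by arm, and several sections show that estimation is intended. This stands. A reader might infer that the pilot would yield only a p-value, and the article does not support that. What remains is that the named method does not match the intended output and no interval is promised.
- **The article does not say that the observed difference will size the full trial.** It says that differences in cure rates will inform the design. A reader might infer more and note the following. Take the interval in the 15% v 35% example, hold control at 15%, and use n = (1.960 + 1.282)² × [p₁(1 − p₁) + p₂(1 − p₂)] / d² for 90% power. The size then runs from about 32 per arm (d = 0.351) to about 1,244 (d = 0.049). That span reflects a pilot of this size at assumed rates. It is the same whether or not a chi-square test is run, so it does not measure this error.
- **No stated decision uses the p-value.** Feasibility rests on recruitment above 60% and retention above 70%, and the lack of power is disclosed. This stands and limits the severity.
- **Stratification is a secondary matter.** Randomisation was stratified and the named test is not. Adjustment is commonly left to the analysis plan, and an unadjusted comparison is not invalid, so this is not a separate fault.

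**Conclusion.** The point holds as a mismatch between method and purpose. The article assigns a test of equal proportions the task of assessing variability, and applies a significance threshold to a difference that it says the study is not powered to detect. The estimates it says it wants are left without a stated interval.

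The relevant size is the uncertainty that should be shown. The 95% half-width for the difference is up to about 18 points, or about 15 points at 15% v 35%. This assumes 120 children assessed, equal arms, a normal-approximation interval and, for the second figure, cure rates that the article does not give.

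This is a lesser correction. The data collected, the conduct of the trial and the recruitment and retention criteria are unaffected. The caution about sizing is conditional: it applies only if the pilot's cure results are used to set the full trial's size.

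**What to change.** Replace the chi-square sentence in Statistical methods with wording such as:

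> The cure rate in each arm and the difference between arms will be reported with 95% confidence intervals, taking the randomisation strata (centre, age, NCS severity) into account where numbers allow; this is estimation only, and any test is exploratory.

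The chi-square test may stay if it is labelled exploratory and no longer described as assessing variability.

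If the cure results are used to size the full trial, take the control-arm rate over its confidence interval together with a pre-specified important difference, and show the resulting range of sample sizes.

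The cost is a few extra lines of analysis and less emphasis on a p-value. No new data and no change to trial conduct are needed.
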